#### Exploratory analysis

To investigate the relationship between radiologic/pathologic parameters of primary NSCLC and prognosis. The consolidation component on CT is defined as an area of increased opacification that completely obscures the underlying vascular markings. Ground-glass opacity is defined as an area of a slight, homogenous increase in density that does not obscure the underlying vascular markings.To accomplish the cost/benefit analysis of sublobar resection.To investigate the outcomes from participants who underwent video-assisted thoracoscopic or open procedures.

### Randomization

The patients who meet the general and pre-operative criteria will undergo surgery, and intra-operative criteria should be evaluated to exclude pre-invasive adenocarcinoma, lymph node involvement, and inadequate surgical margin before randomization. In this procedure, all pre- and intra-operative suspected lymph nodes are biopsied by frozen section sampling before tumor resection to determine whether the patient can be included and randomly assigned in this trial.

The patients meeting the intra-operative criteria will be included and randomly assigned during surgery. The central randomization system will be used with the dynamic minimization random program software; a random number will be assigned to each patient, and the medical center for the surgery will be informed. The patients will be randomly assigned into sublobar resection or lobectomy group by a central computer and further sub-grouped according to age (≤80 or >80 years), pathological type (adenocarcinoma and other types), tumor size (diameter of ≤2 and >2 cm), and 4-year survival index. Once a random number is assigned to a patient, this specific number cannot be re-assigned another one, even if the patient fails to complete the entire study.

### Intervention

#### Surgical approach

Sublobar resection includes two surgical procedures: wedge resection and segmentectomy. For nodules of not more than 2 cm, the surgeon can choose freely between both operation types as long as surgical margin requirements are met. With a maximum tumor diameter of more than 2 cm, segmentectomy should be preferred. Segmental artery and bronchus should be divided individually to be classified as segmentectomy. The surgical margin should be measured on the resected sample and is required to be no less than the lesion diameter for tumors of not more than 2 cm and no less than 2 cm for 2- to 3-cm lesions. Frozen section of the surgical margin is not mandatory. Sublobar resection should be conversed to lobectomy when the frozen section indicates lymphatic metastasis or marginal involvement. Systematic mediastinal lymph node dissection is mandatory if no sampling was carried out prior to randomization. A minimum of three N2 lymph stations are required; nodal levels 2, 4, and 7 should be examined on the right side, and levels 5, 6, and 7 on the left side, along with at least three N1 lymph stations.

The standard of lymph node dissection/sampling applies to the lobectomy arm, as does the surgical margin requirement. When the tumor locates close to a fused fissure, the adjacent lung tissue should be extendedly resected. The distance from the dissection margin to tumor edge must be evaluated in the same manner as with sublobar resections.

#### Adjuvant therapy

For patients with nodal disease, adjuvant chemotherapy is suggested. However, given the advanced age of the study group, the decision should be made by a multi-disciplinary team. The recommended initiation time should be no earlier than 30 days post-operatively, so that surgical complications are not mistaken for adverse events of adjuvant therapy. For patients with incomplete resection, re-resection or radiation is recommended.

### Follow-up

#### Post-operative follow-up

Chest CT scan and QoL evaluation will be performed at follow-up visits every 6 months after operation for 3 years. In case of relapse, survival follow-up by telephone will be proceeded. The pulmonary function will be examined at follow-up visits in 6, 12, and 36 months after operation.

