### Sample size

Sample size was calculated by the PASS (Power Analysis and Sample Size) software, based on 3-year DFS of elderly patients. There were no exact published data about the DFS rate at 3 years of elderly patients with stage I NSCLC [33, 34], and we estimated the DFS rate at 3 years for lobectomy (control group) to be approximately 75 %. DFS rate at 3 years of 60 % for sublobar resection is considered unacceptable. Under our current assumption, the 15 % of non-inferiority margin on DFS at 3 years corresponds to a hazard ratio of 1.78. The sample-size calculation was based on log rank test. The calculated sample size was 339 patients, and event number of 96 was based on an estimated post-operative 3-year DFS rate of 75 %, 10 % non-compliance, 3-year open enrolment period, 3-year follow-up period, and one-sided type I error rate of 0.025 with 90 % statistical power.

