### Recruitment and timeline

This study is planned to start in 10 medical centers across mainland China, and 339 elderly patients with NSCLC at early stage will be recruited. Informed consent should be signed by each patient. Enrollment was activated in December 2015 and is expected to last 3 years. All patients will be included in post-operative and survival follow-ups for 3 years or until death. The actual timeline might be slightly different.

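### Observing DFS for 3 years per patient yields about 73-85 events if the arms are equal, not 96, and log-rank power of about 69-75 %, not 90 %

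*Protocol article*

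**What the plan says.** **Sample size.** The control rate is an assumption: "we estimated the DFS rate at 3 years for lobectomy (control group) to be approximately 75" per cent. For the other arm, "DFS rate at 3 years of 60 % for sublobar resection is considered unacceptable". The margin of 15 points is converted to a hazard ratio of 1.78, and the calculation rests on a log-rank comparison. The outcome is given as follows: "The calculated sample size was 339 patients". With that go 96 events, 10 % non-compliance, a "3-year open enrolment period, 3-year follow-up period", a one-sided alpha of 0.025 and a power of 90 %.

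**Primary endpoint.** DFS runs from randomization to the first of recurrence, metastasis or death, with a 3-year horizon.

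**Post-operative follow-up.** "Chest CT scan and QoL evaluation will be performed at follow-up visits every 6 months after operation for 3 years".

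**Recruitment and timeline.** "All patients will be included in post-operative and survival follow-ups for 3 years or until death".

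**Survival follow-up.** Telephone contact continues to 5 years, but only for patients who have already relapsed.

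**Statistical methods.** The analysis is by intention to treat, with a hazard ratio, its 95 % confidence interval and Cox regression. Survival data are analysed at trial end.

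**The concern.** A log-rank or Cox comparison draws its power from the number of events. The endpoint, follow-up and timeline sections all stop the search for a first DFS event 3 years after each patient enters. The contact to 5 years adds nothing to this count, because those patients have already had their event. With 75 % of patients event-free at 3 years in both arms, at most a quarter can contribute an event, and a quarter of 339 is below 96.

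The number of events and the power attached to it are also inconsistent with each other, before follow-up is considered at all. If both problems stand, the chance of missing non-inferiority when the two operations are truly equivalent is about 25-31 %, not the 10 % that the plan states.

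**Working it through.** **Inputs.** From the article: 3-year DFS 75 % (control) and 60 % (unacceptable); one-sided alpha 0.025; 339 patients; 96 events. Assumed because the article does not say: exponential DFS, uniform accrual, 1:1 allocation, and 10 % non-compliance acting as loss. The way that loss enters is not stated, so a range is shown.

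**Step 1: the margin.** ln 0.60 / ln 0.75 = 1.776, which agrees with 1.78. Its logarithm is 0.574.

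**Step 2: the stated events and power.** Schoenfeld: d = 4 (z_alpha + z_power)² / (ln HR)².
- 80 % power: 4 × (1.960 + 0.842)² / 0.574² = 95.2, rounded up to 96.
- 90 % power: 4 × (1.960 + 1.282)² / 0.574² = 127.5 (about 126.4 with HR 1.78).
- Freedman's formula gives 134-135 for 90 %.

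So 96 is the Schoenfeld number for 80 % power. Conversely, power = Φ(√(96/4) × 0.574 − 1.96) = 80 %.

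**Step 3: events from 3 years per patient, both arms at 75 %.** The event hazard is λ = −ln 0.75 / 3 = 0.0959 per year. With loss hazard μ, P(event) = λ/(λ+μ) × (1 − e^(−3(λ+μ))).

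| Loss | μ | P(event) | Events from 339 | Power |
|---|---|---|---|---|
| None | 0 | 0.250 | 84.8 | 75 % |
| 10 % by year 3 | 0.0351 | 0.238 | 80.6 | 73 % |
| 10 % per year | 0.1054 | 0.216 | 73.2 | 69 % |

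Power is Φ(√(d/4) × 0.574 − 1.96). Removing 10 % of patients outright gives 305 × 0.25 = 76 events and 71 %, inside this range. The chance of seeing 96 or more events is 9 % with no loss and 3 % or less with either loss rate in the table.

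**Step 4: splitting the gap.** From 90 % to about 80 % is the mismatch in Step 2. From about 80 % to 75 %, 73 % or 69 % is the shortfall below 96 events, a further 5, 7 or 11 points.

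**Step 5: can the origin of 339 and 96 be recovered?** With 80 % power and 10 % annual loss, two routes fit.
- Common closing date (3 years' accrual plus 3 years), 75 % in both arms. With k = λ+μ = 0.2013, P(event) = λ/k × [1 − (e^(−3k) − e^(−6k))/(3k)] = 0.281, and N = 95.2/0.281 = 339.
- Fixed 3 years per patient, 75 % and 60 %. The event probabilities are 0.216 and 0.348, mean 0.282, and N = 95.2/0.282 = 338.

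At 90 % power, 339 can be approached alone, through Freedman with 75/60 rates and a common close (134/0.439 = 306; 306/0.9 = 340). That route carries 134 events, not 96.

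**Step 6: a common closing date, both arms at 75 %.** With no loss, P(event) = 1 − (0.75 − 0.5625)/0.2877 = 0.348, giving 118 events and 88 % power. With 10 % lost per year, 0.281 × 339 = 95 events and 80 %. Even this schedule does not reach 90 %.

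**The case against.** A reader might infer that the sample size counted events out to year 6 and that the follow-up text then cut them off at year 3. An enrolment period matters to such a calculation mainly when patients are followed to a common date, and a non-inferiority trial is normally powered with equal arms. But the article never says so, its 3-year follow-up period can be read as per patient, and Step 5 shows that a fixed 3 years with 75/60 rates gives almost the same pair of figures. The 6-year count is one candidate only. Both routes also need 10 % loss per year, and the article gives no time unit.

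It can also be said that 96 is attainable. If sublobar DFS were really 60 %, 3-year observation would give about 96-110 events, depending on loss. That is true, but it is the scenario that the trial should reject, so it does not support the power to show non-inferiority.

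A direct comparison of 3-year DFS rates against 15 points would have about 86-89 % power (339 or 305 patients). This limits the finding to the test named. The article specifies log-rank for the sample size and a hazard ratio for the analysis.

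The Discussion mentions recurrence and metastasis at 5 years as well as 3, so the text is not wholly uniform about the horizon. The endpoint and follow-up sections are nevertheless explicit, and no 5-year follow-up of relapse-free patients is described.

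Finally, a reader might think that the analysis would wait for a 96th event that never comes. Nothing in the article makes the analysis event-driven; Statistical methods places it at trial end.

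**Conclusion.** The point holds in this form: the stated 339 patients, 96 events and 90 % power do not fit together, and do not fit 3-year observation when the arms are equal. That schedule gives about 73-85 expected events and 69-75 % log-rank power. Of the 15-21 points lost from 90 %, about 10 arise because 96 events carry only about 80 % power, and 5-11 arise from the observation window. Correcting the power label to 80 % would therefore still overstate it.

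The result rests on exponential DFS, uniform accrual (for the common-close figures), 1:1 allocation, 75 % DFS in both arms and the loss range shown. It does not rest on any view of how 96 was derived, which the article leaves open.

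**What to change.** Reconcile the primary endpoint, Post-operative follow-up, Sample size, and Recruitment and timeline sections. Two options are open.

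1. **Keep 3-year observation.** Restate the expected events (about 73-85) and the log-rank power (about 69-75 %) with equal arms, and give the event rates, the loss rate with its time unit, and the observation window used. This costs wording only, but it makes the lower power visible.
2. **Collect DFS status on all patients to a common closing date** and remove the 3-year cut from the endpoint. State about 95-118 events and 80-88 % power, depending on loss. The cost is extra data collection for early enrollees. The article reports that enrolment was not yet complete, so this could still be planned when it was written.

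Under either option, correct the pairing of 96 events with 90 % power: about 80 % for 96 events, or about 127 events for 90 %.

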#### Survival follow-up

Telephone follow-up will be used to contact patients every 3 months if recurrence occurred until 5 years or death, to acquire subsequent medical management and death data. The following information should be obtained at each interview: survival state; death date and cause; disease situation, including recurrence date; detailed information about therapeutic strategy, including the first- and second-line therapies, and any other subsequent operations.

### Adverse event reporting

A data and safety monitoring committee will monitor patient safety, and all ongoing serious adverse events will be closely followed until stabilization. The complications occurring after operation until discharge, or within 30 days post-operation in discharged patients, are considered post-operative complications; death during the same period is defined as peri-operative death. Post-operative complications are described according to the Common Terminology Criteria for Adverse Events 4.1 published (CTCAE version 4.1) by National Cancer Institute of the US, reported, classified, and recorded into case report form (CRF).

### Sample size

Sample size was calculated by the PASS (Power Analysis and Sample Size) software, based on 3-year DFS of elderly patients. There were no exact published data about the DFS rate at 3 years of elderly patients with stage I NSCLC [33, 34], and we estimated the DFS rate at 3 years for lobectomy (control group) to be approximately 75 %. DFS rate at 3 years of 60 % for sublobar resection is considered unacceptable. Under our current assumption, the 15 % of non-inferiority margin on DFS at 3 years corresponds to a hazard ratio of 1.78. The sample-size calculation was based on log rank test. The calculated sample size was 339 patients, and event number of 96 was based on an estimated post-operative 3-year DFS rate of 75 %, 10 % non-compliance, 3-year open enrolment period, 3-year follow-up period, and one-sided type I error rate of 0.025 with 90 % statistical power.

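### At the stated margin and one-sided 0.025, 96 events give about 80 % power, not the stated 90 %, and 339 patients do not reach 90 % either

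*Protocol article*

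**What the plan says.** All the inputs stand in the Sample size section of the protocol article.

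- Control arm: "we estimated the DFS rate at 3 years for lobectomy (control group) to be approximately 75" %.
- Limit of acceptability: "DFS rate at 3 years of 60 % for sublobar resection is considered unacceptable".
- Margin: "the 15 % of non-inferiority margin on DFS at 3 years corresponds to a hazard ratio of 1.78".
- Method: "The sample-size calculation was based on log rank test".
- Result: "The calculated sample size was 339 patients, and event number of 96 was based on an estimated post-operative 3-year DFS rate", followed by "75 %, 10 % non-compliance, 3-year open enrolment period, 3-year follow-up period".
- Error rates: "one-sided type I error rate of 0.025 with 90 % statistical power".

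The 90 % appears only there. The abstract says that 339 subjects follow from power calculations and gives no power figure.

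**The concern.** The number of events for a log-rank non-inferiority test is fixed by alpha, power, margin and allocation. Accrual, follow-up and loss affect only how many patients are needed to produce those events. The stated 96 can therefore be checked directly against the stated 90 %, and it looked too small for a margin of 1.78 at one-sided 0.025.

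What is at stake is the false-negative risk on the primary question. A reader takes it from the protocol that a truly non-inferior sublobar resection would be missed one time in ten. If 96 events is the target, it would be missed about one time in five, and an inconclusive result would be judged against the wrong expectation. The type I error and the margin are not affected.

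**Working it through.** **Inputs.** From the Sample size section: one-sided alpha 0.025 (z = 1.960), 3-year DFS of 75 % and 60 %, margin hazard ratio 1.78, 96 events, 339 patients, 10 % non-compliance, 3-year enrolment, 3-year follow-up, 90 % power. Assumed here: 1:1 allocation (the ratio is not stated, and unequal allocation would need more events), true hazard ratio 1, exponential DFS, uniform accrual.

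**Step 1: margin.** ln(0.60)/ln(0.75) = 1.7757, which rounds to the stated 1.78. Its logarithm is 0.5742. This figure is reproduced.

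**Step 2: events (Schoenfeld).** d = 4 × (z_alpha + z_power)² / (ln HR)².

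- 90 % power: 4 × (1.960 + 1.282)² / 0.5742² = 127.5, so 128 events.
- 80 % power: 4 × (1.960 + 0.842)² / 0.5742² = 95.2, so 96 events.

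The stated 96 is reproduced at 80 %, not at 90 %. With the rounded 1.78 the figures are 127 and 95. Freedman's formula gives 134 to 135 events for 90 %.

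**Step 3: power at 96 events.** Φ(√(96/4) × 0.5742 − 1.960) = Φ(0.853) = 80.3 %. It is 80.6 % with 1.78, and about 78 % by Freedman. Even at one-sided 0.05 it would be about 88 %, and 90 % would need 104 events.

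**Step 4: power of 339 patients.** The DFS hazard is −ln(0.75)/3 = 0.0959 per year in both arms. With loss hazard η and k = 0.0959 + η, the probability of an observed event is (0.0959/k) × [1 − mean of exp(−kt)], where t is uniform on 3 to 6 years, or fixed at 3 years. Multiplying by 339 gives the expected events, and the formula of step 3 gives the power.

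| Reading of the 10 % and of observation time | P(event) | Events from 339 | Power |
|---|---|---|---|
| 10 % lost per year, 3–6 years | 0.2809 | 95.2 | 80.0 % |
| Flat 10 % removed, 3–6 years | 0.9 × 0.3482 | 106 | 84 % |
| 10 % lost by 3 years, 3–6 years | 0.3234 | 110 | 85 % |
| 10 % lost by 6 years, 3–6 years | 0.3355 | 114 | 86 % |
| No loss, 3–6 years | 0.3482 | 118 | 88 % |
| No loss, 3 years fixed | 0.2500 | 85 | 75 % |
| 10 % lost per year, 3 years fixed | 0.2160 | 73 | 69 % |

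No row reaches 90 %.

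**Step 5: where 339 may come from.** Under the first row, 80 % power needs 95.23/0.2809 = 339.0 patients, which is the stated number. At 90 % the same row needs 127.5/0.2809 = 454. Other readings with 3–6 years of observation give, for 80 % power, 284 (10 % lost by 6 years), 294 (by 3 years) or 304 (single inflation). For 90 % they give 380, 394 and 407.

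**The case against.** The strongest objection concerns the patient number. The text speaks of non-compliance. It does not mention loss to follow-up and does not say whether the 10 % is annual or total. A reader might infer from the exact match at 339.0 that the 10 % was entered as annual loss and that 339 patients carry 80 % power. The documents do not establish this. The match comes from one reading among several, and on total-loss readings 339 patients would give about 84 to 86 %. This stands: the match suggests that the calculation was run at 80 %, but does not prove it.

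The same caution applies in the other direction. The first row needs 3 to 6 years of observation per patient. The Recruitment and timeline section can be read as 3 years for everyone, the Follow-up section schedules chest CT for 3 years, and the primary endpoint is DFS at 3 years. On that reading 339 patients give about 69 to 75 %, so 80 % cannot simply be certified for 339 patients.

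A further defence is that putting 60 % DFS in the sublobar arm brings some 90 % calculations near 339 patients. Those still need 127 to 128 events, not 96. They also conflict with the stated 75 % and place the experimental arm at the margin, where power for non-inferiority is not evaluated.

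Finally, the text is a condensed article whose analysis plan is not shown. That would excuse an omission, but here a figure stands beside the inputs that contradict it. None of these objections reconciles 96 events with 90 % power.

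**Conclusion.** The point holds for the event target without qualification: 96 events give 80.3 % power on the stated inputs, and 90 % needs about 128. The shortfall is 32 events, or a false-negative risk of about 20 % where 10 % is stated. This rests on a true hazard ratio of 1, equal allocation and the usual log-rank approximation. Freedman's formula and unequal allocation would both widen the gap.

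For the 339 patients, the conclusion is that 90 % is not reached on any reading of the 10 % with 75 % DFS in both arms. The actual power lies between about 69 % and 88 %, depending on how the 10 % and the observation time are meant. That the sponsor used annual loss is a plausible inference and no more. A reader might also infer that the abstract repeats the wrong power. It does not, because it gives no power figure.

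**What to change.** In the Sample size section:

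1. Change the stated power from 90 % to 80 % for the 96-event target.
2. State how the 10 % non-compliance was entered (annual rate, total loss or single inflation) and what observation time per patient was assumed (fixed 3 years, or 3 to 6 years).
3. Give the power of 339 patients on that basis.

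This costs one corrected figure and two clarifying sentences, and no patients are added. The stated power becomes less favourable.

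If 90 % is the intended design, restate the event number as about 128 and recalculate the sample size. With 3 to 6 years of observation that is about 380 to 454 patients, depending on the loss assumption. With a fixed 3 years it is about 510 (127.5/0.25, no loss) to 590 (10 % lost per year). The article says that enrolment has begun but is not complete, so the sponsor can still make this choice openly, before the survival analysis planned for trial end. The figures 96 and 90 % should not stand together.

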### Recruitment and timeline

This study is planned to start in 10 medical centers across mainland China, and 339 elderly patients with NSCLC at early stage will be recruited. Informed consent should be signed by each patient. Enrollment was activated in December 2015 and is expected to last 3 years. All patients will be included in post-operative and survival follow-ups for 3 years or until death. The actual timeline might be slightly different.

### Database management

A data management plan is drafted in detail before analysis implementation, according to research scheme characteristics and CRF collection. The draft plan includes data quality audit, electronic database establishment, and acquisition method for complete and expected data. Data quality will be checked after primary data input into the database and verification of completely consistent entries. Data consistency and logistics should be confirmed by a combination of artificial audit and computer program. Any doubts raised during this period should be resolved by researchers, and the corresponding update and modification will be carried out by database specialists. The assessment program should be repeated multiple times to avoid doubts, and all modified data and updates recorded and archived. The CRF table will be used to record all data with blue- or black-ink ballpoint pen in clear handwriting. Correction fluid or tape is prohibited during the whole process. Researchers have to ensure CRF table authenticity.

